### Procedure

#### Recruitment and consent process

Willing home visitors will be recruited and consented after site presentations about the study goals, procedures, and potential benefits and risks. Home visitors will be educated on the family inclusion and exclusion criteria. Home visitors are expected to routinely screen mothers for depression and provide mental health referrals to those who screen positive for depression on the *EPDS*. Home visitors will use this standard practice to identify eligible adolescent mothers for recruitment, as it increases the generalizability of our findings. Home visitors will provide those with *EPDS* scores of ≥ 8 with two options: (i) study participation or (ii) referral for mental health services in the community. Home visitors will present a script to eligible families that include the study goals, treatment, and potential benefits and risks. The home visitor will provide each interested family’s contact information to a research assistant who will call the family to schedule a meeting to review the consent and assent forms and obtain written informed consent from all willing participants. Families will be informed that participation is voluntary and they can receive home visiting regardless of whether or not they decide to participate in the study.

#### Study measures

Treatment implementation practices and both process and outcome measures will guide the translation of research to clinical practice. Process measures include indicators of feasibility (knowledge, adherence, quality of delivery, and retention) and acceptability (home visiting staff and family responsiveness). The process measures were selected using criteria by Mowbray, Holter, Teague, and Bybee (2003) [46]. The study measures are presented in Table 1.

**Table 1 Tab1:** Study measures by aim, construct, respondent, and time point

Construct	Measure	Respondent			Time point		
		Mother	Family	Home visitor	O_1_	O_2_	O_3_
1. Feasibility and acceptability of implementing the treatment in HV.							
Knowledge	Pass test on the use of video software.			X	X		
	Percent of eligible families identified.^a^			X		X	
Adherence	Percent of families educated in use of video software.^b^			X		X	
	Percent of visits with coping skill reinforcement.^b^			X		X	
Home visiting Staff responsiveness	Percent of training sessions attended.^a^			X	X		
	Percent of supervision sessions attended.			X		X	
	Percent of implementation meetings attended.^a^			X		X	
	Satisfaction, usefulness, and relevance of family support team responsibilities from focus groups.			X			X
2. Feasibility and acceptability of implementing treatment with families.							
Quality of delivery	Working Alliance Inventories—therapist and client versions [49, 50].^c^	X	X			X	X
Retention	Percent of families who complete treatment.	X	X				X
Family responsiveness	Percent of completed homework assignments.	X	X			X	
	Satisfaction questionnaire developed by team.	X	X				X
3. Evidence of clinical effectiveness of the treatment.							
Depression	SCID-V Depression Module [55]; NIMH DISC-Y and DISC-P Mood Module for those under 18 [56].^d^	X				X	
	Beck Depression Inventory-II (BDI-II) [57].^d^	X				X	X
Emotion regulation	Emotion Regulation Questionnaire (ERQ) [58], ERQ Child and Adolescent Version for those under 18 [59].	X	X			X	X
Parental empathy	Adult Adolescent Parenting Inventory-II (AAPI-II) [60].	X				X	X
Family functioning	Protective Factors Survey, Family Functioning/Resiliency subscale [61].	X	X			X	X

^a^Co-investigators will monitor recruitment of families and record HV staff attendance

^b^Based on home visitor report to the therapist

^c^Monitoring measure, also completed by therapist, at the end of therapy session 6

^d^Monitoring measures completed at the end of therapy sessions 4 and 8; diagnostic interviews will only be used for adolescent mothers with increased BDI-II scores

Study measures will be completed at three time points: home visitor baseline (O_1_), family baseline and treatment (O_2_), post-treatment and the 2-month follow-up (O_3_). Home visitor baseline measures will include demographic information (age, level of education, and tenure) and turnover intention within 12 months. For knowledge of HIPAA-compliant video-based communication technology, home visitors will demonstrate its use on their laptops and cell phones. For knowledge of family eligibility/inclusion and exclusion criteria, co-investigators will monitor home visitor identification of eligible families, record discrepancies and resolutions, and record the percent of eligible families recruited. Family baseline measures will be completed in O_2_, within 2 weeks prior to the first therapy session. Demographic information will be collected on adolescent mothers, infants (age only), and family members. Monitoring measures will be completed in O_2_. Home visitor post-treatment measures (completed within a month of their last family completing treatment), family post-treatment measures (completed at the end of the final therapy session), and the 2-month family follow-up will be completed in O_3_.

#### Intervention

The treatment model consists of 10, 30-min, family therapy sessions that are concurrent with ongoing home visits. The sessions will occur on a weekly basis. The systemic treatment model is informed by dialectical behavior therapy (DBT) skills for adolescents and includes coping skills that address three types of regulation: cognitive, emotion, and behavior [29]. A PI received written permission from Drs. [name] and [name] to adapt some skill teaching content from their model for use in the study treatment.

Scripted statements will be developed for use by home visitors in home visits to reinforce maternal use of coping skills that align with national home visit content. Home visitors will serve as the in-home, family support team member. In this role, they will participate in parts of the first and final therapy sessions, educate families in how to use HIPAA-compliant video-based communication technology, reinforce maternal use of coping skills during home visits, and participate in weekly supervision with the therapist to discuss coping skill reinforcement and maternal progress. Home visitors will participate in the first therapy session to explain their role as a family support team member. Home visitors will participate in the last therapy session to promote adolescent mothers’ continued use of the coping skills.

### Planned analyses

The planned analyses are organized by study aim. For the first aim, univariate statistics will be used to characterize indicators of feasibility (knowledge and adherence). For knowledge of HIPAA-compliant video-based communication technology, home visitors will demonstrate their understanding of setting up and using the software on a computer and cell phone. The average number of times it takes home visitors to correctly complete this task will be calculated. Feasibility will be demonstrated by all home visitors successfully accessing the software by the second attempt. For knowledge of family eligibility, a percentage will be obtained for home visitor accuracy in identifying eligible families for participation by dividing the number of eligible families listed in the site’s database that are regularly receiving home visits. Feasibility will be demonstrated by home visitors correctly identifying at least 80% of eligible families for study participation. For adherence, the percentage of families who are educated in use of HIPAA-compliant video-based communication technology will be calculated and the ratios for actual to expected coping skill reinforcement will be calculated for each home visit and summarized overall. Feasibility will be demonstrated by home visitors educating all participating families in how to use the HIPAA-compliant video-based communication software and home visitor reinforcement of at least 80% of coping skills in home visits. For acceptability (HV staff responsiveness), univariate statistics and qualitative data analytic methods [47] will be used. For HV staff responsiveness, attendance rates will be calculated for the training, implementation meetings, and supervision sessions. Acceptability will be demonstrated by HV staff attendance at all required training activities. Home visitors will participate in focus groups held at each of the two Federal HV Program sites (see Table 1). Three experienced independent coders will code focus group transcriptions. A thematic analytic approach [48] will be used due to the semi-structured, open-ended focus group questions. The independent coders will use traditional open coding to code participants’ responses to the questions. Thematic analysis will be conducted using inductive coding [48]. The independent coders will schedule consensus meetings to discuss codes and resolve discrepancies. They will group the codes into categories to create themes, which will be identified through consensus. This iterative process will allow the independent coders to formalize the themes. The emergent themes will be identified and summarized [47].

For the second aim, univariate statistics (e.g., means, proportions, 95% confidence intervals) will be used to characterize family baseline characteristics and indicators of feasibility (quality of delivery and retention). Bivariate statistics will be used to explore the associations of family baseline characteristics with indicators of feasibility. For quality of delivery, average therapist scores and family scores will be calculated for each subscale on the *Working Alliance Inventory-Short Revised* (Therapist and Client versions—see Table 1) [49, 50] after family therapy sessions 6 and 10. High quality of delivery will be determined by *Working Alliance Inventory-Short Revised* Therapist and Client mean scores of 5 and above on each subscale at post-treatment. For retention, the total number of attended family therapy sessions will be calculated. Ratios for the actual to expected number of family therapy sessions will be calculated. High retention will be evidenced by families attending 70% of the expected number of sessions. For acceptability (family responsiveness), univariate statistics and qualitative data analytic methods [47] will be used. For family completion of homework assignments, the percentage of completed assignments will be calculated overall and for each coping skill module. Family completion of one homework assignment per coping skill module will suggest the treatment is acceptable to families. For family satisfaction, averages will be calculated for multiple-choice items and three independent experienced coders will code responses to the open-ended questions [47]. A thematic analytic approach [48] will be used due to the semi-structured, open-ended questions on the satisfaction questionnaire. The independent coders will use traditional open coding for the open-ended questions and free text responses. Thematic analysis will be conducted using inductive coding [48]. The independent coders will schedule consensus meetings to discuss codes and resolve discrepancies. Codes will be grouped into categories to create themes, which will be identified through consensus. The emergent themes will be identified and summarized [47].

For the third aim, the internal consistency of each outcome measure will be assessed. Basic sample statistics (e.g., means, proportions, 95% confidence intervals) will be used to characterize family baseline, post-treatment, and follow-up measures. Difference scores will be calculated, and treatment impacts on outcomes will be explored from baseline to post-treatment to follow-up. Evidence of effectiveness will be demonstrated at follow-up by significant reductions in depressive symptoms and emotional suppression, and significant improvements in cognitive reappraisal, parental empathy, and family functioning. We will compare changes in *EPDS* scores of previously enrolled adolescent mothers to those of adolescent mothers who received the study treatment at 6 months post-enrollment in the HV program. Evidence of effectiveness will be demonstrated by significantly lower *EPDS* scores in adolescent mothers who received the study treatment.

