**Methods:**

This study protocol includes a description of an implementation-effectiveness hybrid trial design that will include 12 depressed adolescent mothers and their family members and a historical comparison group of 12 previously enrolled adolescent mothers.

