Second, we will explore the feasibility and acceptability of the treatment model among depressed adolescent mothers and their families. Evidence of feasibility with this population will be demonstrated by quality of delivery (strong therapist-family working alliance) and retention of at least 80% of families. Evidence of acceptability with this population will be demonstrated by high family responsiveness through completion of homework assignments and report of high satisfaction with treatment.

Finally, we will explore preliminary impacts of the treatment on maternal depressive symptoms and parental empathy, and family emotion regulation and family functioning at 2 months post-intervention. We hypothesize that mothers will show a clinically meaningful reduction in depressive symptoms and improvements in parental empathy at 2 months post-intervention. When compared to adolescent mothers who were previously enrolled in home visiting, those who received the study treatment will show preliminary evidence of a greater reduction in depression. We also hypothesize that families will show clinically meaningful improvement in emotion regulation and family functioning.

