### Participant selection

The two Federal HV Program sites employ a total of 10 home visitors and serve about 44 families in three counties in New England. Eight home visitors and 12 adolescent mothers (pregnant *and* post-delivery), ages 13–25 years old, and their family members (six families per site) will be recruited. “Family member” is defined as one who is biologically related to the adolescent mother or a significant close other with whom she is not biologically related. The sample size was determined in consultation with our external community stakeholders. They recommended that we implement the protocol in two different Federal HV Program sites with a small number of families (i.e., 6 per site) in order to obtain early evidence of feasibility (e.g., implementation strategies such as staff training, research strategies such as family recruitment and retention) and acceptability (e.g., perceived agency burden, family receptivity) in preparation for larger studies of potential effectiveness and scalability.

This study also includes a historical comparison comprised of 12 depressed adolescent mothers who were previously enrolled in home visiting and have similar characteristics to those who will be recruited for the study. We will match the previously enrolled adolescent mothers to intervention group mothers based on scores of the *Edinburgh Postnatal Depression Scale* (*EPDS*) [45] administered at equivalent time intervals, maternal age, home zip code, pregnancy trimester or infant age for postpartum adolescents, relationship status, average annual income, and highest level of education.

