The inclusion of a community advisory board will help shape the interpretation and use of the findings to prepare the final intervention for a larger study. The valuable feedback will help us to refine the treatment model, which strengthens its potential effectiveness in future studies. As previously mentioned, the sample size was determined in consultation with our external community stakeholders and will allow us to obtain evidence of feasibility and acceptability in preparation for larger studies of potential effectiveness and scalability. Therefore, our feasibility and acceptability aims provide a rationale for the sample size [53]. Since this small pilot study is not powered to test statistical differences, the results may not reveal a significant decrease in maternal depressive symptoms. Data on the therapeutic working alliance, family functioning, emotion regulation, and family satisfaction will also be useful in highlighting the perceived value of the intervention. We will compare and evaluate the consistency of the qualitative and quantitative data to inform decisions about needed changes to the study protocol and design. Therefore, the results of this pilot study will be used to inform our future research on the potential benefits of the integrated treatment model on home visiting service delivery and improving maternal mental health outcomes.

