### Limitations

The current study protocol has three limitations. First, our study is not a randomized controlled trial. Although, we plan to eventually conduct a randomized controlled trial of the study intervention. Second, the small sample size included in this feasibility and acceptability study limits the impact and generalizability of our results. Furthermore, it is entirely possible that the results will yield trends rather than statistically significant impacts on outcomes. Pilot studies are used to assess the feasibility of an intervention for a larger scale study, and the use of pilot study effect size for sample size estimation can lead to type I and II errors [54]. For these reasons, our results will be used to inform a larger scale study but not to test impact. The preliminary work outlined in this protocol will help determine if it is feasible and acceptable to implement the study intervention within the context of home visiting. Finally, the maternal characteristics in the exclusion criteria further may limit the generalizability of our results to home-visited populations that have these characteristics.

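### Aim 3 lets statistical significance demonstrate effectiveness, although the protocol says the study is not powered for such tests and will not test impact

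*Protocol article*

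**What the plan says.** Planned analyses (third aim) contains two decision rules. The first covers change from family baseline to follow-up: "Evidence of effectiveness will be demonstrated at follow-up by significant reductions in depressive symptoms and emotional suppression", with significant improvement also required in cognitive reappraisal, parental empathy and family functioning. That makes five outcomes. The second compares groups: effectiveness is demonstrated by significantly lower EPDS "scores in adolescent mothers who received the study treatment" than in the previously enrolled mothers.

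Other sections of the article set a different standard:

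- Study purpose and aims presents Aim 3 as exploratory and hypothesises that "mothers will show a clinically meaningful reduction in depressive symptoms". It expects only preliminary evidence from the historical comparison.
- Participant selection gives the basis for the numbers: "The sample size was determined in consultation with our external community stakeholders". The Abstract gives the numbers themselves: "12 depressed adolescent mothers and their family members and a historical comparison group of 12 previously enrolled adolescent mothers".
- Discussion: "Since this small pilot study is not powered to test statistical differences, the results may not reveal a significant decrease in maternal depressive symptoms".
- Limitations: "our results will be used to inform a larger scale study but not to test impact".

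**The concern.** A rule under which a significant result demonstrates effectiveness is a test of impact, whatever the surrounding text calls it. The article therefore states a test, says the study cannot support it, and says it will not be made. The rule also drops the clinically meaningful standard on which the hypotheses are built.

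The more serious consequence is a favourable result. If a pre-post p-value falls below the threshold, the plan as written licenses an effectiveness claim from an uncontrolled change in mothers who entered because their EPDS was raised. The pilot is meant to inform a larger study, so such a claim could carry over into how that study is justified and planned. In the other direction, a moderate benefit could easily miss significance and be read as no evidence, when an estimate with its interval would be more informative.

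**Working it through.** **Plan's own figure.** There is none to reproduce. The article gives no effect size, SD, significance level or power, and bases the sample on stakeholder consultation and the feasibility and acceptability aims.

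**Side-by-side reading.**

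| Section | Standard for Aim 3 |
|---|---|
| Study purpose and aims | Clinically meaningful change; preliminary evidence for the group comparison |
| Planned analyses | Statistical significance, in both rules |
| Discussion | Not powered for statistical differences; significance may not appear |
| Limitations | Trends possible; results not used to test impact |

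The last two rows concern the chance of missing significance and the use of the results. Neither withdraws the rule in the second row.

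**Inputs for the size check.** From the article: 12 treated and 12 historical mothers; no randomisation (Study design); entry at EPDS of 8 or more (Inclusion criteria); a retention target of at least 80% (Study purpose and aims). Since 0.80 × 12 = 9.6, that target means about 10 mothers. Assumed: two-sided 5% level, t-tests, and the effect sizes shown.

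**Pre-post, one maternal outcome.** Let d be the mean change divided by the SD of the change score. Power is approximately P(T > t₀.₉₇₅,ₙ₋₁), where T is noncentral t with n − 1 degrees of freedom and noncentrality d√n. The opposite tail is negligible.

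- n = 12, critical value 2.201. At d = 0.5 the noncentrality is 0.5 × 3.464 = 1.73 and power is 35%. At d = 0.8 it is 2.77 and power is 71%. Power of 80% needs d = 0.89.
- n = 10, critical value 2.262. Power is 29% at d = 0.5 and 62% at d = 0.8. Power of 80% needs d = 1.00.

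These are change-score SDs. In raw-score SDs, d = d_raw / √(2(1 − r)), where r is the baseline to follow-up correlation. For d_raw = 0.5 and n = 12:

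- r = 0.5: d = 0.50, power 35%
- r = 0.7: d = 0.65, power 53%
- r = 0.8: d = 0.79, power 70%

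**Between groups, 12 versus 12, unpaired.** The noncentrality is d / √(1/12 + 1/12) = d / 0.408, with 22 degrees of freedom and critical value 2.074. At d = 0.5 it is 1.22 and power is 22%. At d = 0.8 it is 1.96 and power is 47%. Power of 80% needs d = 1.20. An analysis by matched pairs would instead follow the n = 12 line above, in SDs of the pair difference.

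**Selection.** Entry requires a raised EPDS, and the pre-post rule has no concurrent control. Natural recovery and regression to the mean therefore both push depressive symptoms towards improvement without any treatment effect. Table 1 measures pre-post depression on the Beck Depression Inventory-II (BDI-II), not the EPDS. The family baseline is taken within two weeks before the first session and is separate from the EPDS screen. Some regression may already have happened by then, so only the direction follows from the documents.

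**The case against.** The best defence is that the article is candid. Aim 3 is exploratory, the non-randomised design and small sample are listed as limitations, and the sample size is justified by feasibility and acceptability. Means with 95% confidence intervals and difference scores are already planned. All of this is true and lowers the severity. It does not remove the conflict, because the two decision sentences stay in force.

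Several stronger readings are tempting, and the documents do not support them.

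- *A null result would also contradict the Discussion and Limitations.* It would not; both sections openly anticipate it. The conflict lies in treating a significant result as demonstration of effectiveness.
- *Regression to the mean can be put in points.* A figure could be produced for the EPDS, but only from an assumed population mean, SD and retest correlation, and for a scale that is not the pre-post depression measure. Matching the historical mothers on EPDS partly addresses this bias in the group comparison. The other four pre-post outcomes are not selection variables.
- *All five outcomes must be significant, or any one suffices.* The text says neither. Joint power or false-positive rates would also require independence between related measures, two of which come from one questionnaire.
- *Every pre-post outcome rests on 12 people.* Table 1 has family members also completing the emotion regulation and family functioning measures, so the 12-pair figures apply strictly to maternal outcomes.
- *The clinically meaningful threshold is missing.* A numerical threshold may stand in the full protocol or SAP, so its absence from the article is not held against the plan.

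**Conclusion.** The concern holds as an internal contradiction that should be fixed, not as a flaw in the design. Planned analyses makes significance the criterion of effectiveness twice. Discussion and Limitations disclaim that use, and the hypotheses set a different criterion. Followed literally, the plan permits an effectiveness claim from an uncontrolled change that could partly reflect selection or natural recovery.

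Power for the maternal pre-post outcomes ranges from low at moderate effects to fair at large ones. Power for the group comparison is low unless the effect is very large. These figures rest on the assumed two-sided 5% level, t-tests and illustrative effect sizes. One should not infer that a useful treatment would most likely fail: at 0.8 change-score SDs, 12 pairs would more often succeed. The contradiction itself needs none of these assumptions.

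**What to change.** In Planned analyses, third aim:

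1. Delete both sentences that make significant results the demonstration of effectiveness.
2. State that mean change per outcome and the between-group EPDS difference will be reported with 95% confidence intervals. The existing sentence on summary statistics needs only a small extension.
3. Judge these estimates against the clinically meaningful change named in the Aim 3 hypotheses.
4. Describe pre-post results as change, not impact, and draw no effectiveness conclusion from p-values.

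The cost is wording only. Sample size, measures, visits and data collection are unchanged. The sponsor gives up a significance claim that the article already disclaims.

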### Inclusion criteria for home visitors and families

Home visitors must be willing to participate in the study. Home visitors must intend to remain in their current jobs for at least 12 months. Finally, home visitors must be fluent in English since the training on study responsibilities, treatment model, implementation meetings, and supervision sessions will be carried out in this language.

Adolescent mothers, ages 13–25, in the first trimester of pregnancy through 18 months postpartum with *Edinburgh Postnatal Depression Scale* (*EPDS*) [45] scores of ≥ 8 will be recruited for study participation. At least one of the adolescent mother’s family members must be willing and available to participate in eight of the 10 video-based family therapy sessions. All families must be fluent in English and have a consistent Internet access (i.e., subscribe to an Internet service provider and do not experience weekly disruptions in service) on a cell phone or computer equipped with a camera and microphone.

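### The historical EPDS comparison is timed from home visiting enrollment, not from treatment, so a treated mother's reading can fall during or before therapy

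*Protocol article*

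**What the plan says.** The Planned analyses section (third aim) sets the EPDS changes of previously enrolled mothers against "to those of adolescent mothers who received the study treatment at 6 months post-enrollment in the HV program". A significantly lower EPDS in the treated mothers is then to count as showing effectiveness. This is the only between-group comparison in the article. Table 1 does not list the EPDS among the third-aim measures, so it gives no other time point for it.

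Therapy runs on its own clock. Under Intervention, "The treatment model consists of 10, 30-min, family therapy sessions that are concurrent with ongoing home visits", and "The sessions will occur on a weekly basis". The other third-aim measures follow that clock. Family baseline is taken "within 2 weeks prior to the first therapy session", post-treatment measures at the final session, and follow-up 2 months later (Study measures).

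Entry to the study is triggered by routine EPDS screening of HV clients (Recruitment and consent process), not by joining the program. The sites already "serve about 44 families in three counties in New England". The first-aim accuracy measure takes its eligible families from those in the site database who are receiving regular visits. Mothers qualify "in the first trimester of pregnancy through 18 months postpartum with" an EPDS of 8 or more. Neither the inclusion nor the exclusion criteria mention time since HV enrollment.

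**The concern.** An outcome reading has to come after the exposure that it is meant to judge. Here the reading is fixed by one date (HV enrollment) and the exposure by another (study entry after a positive screen), and no rule links the two. A mother who has been with the program for some time when she screens positive may pass her 6-month mark during therapy or before session 1. If her qualifying screen also comes after month 6, her EPDS change ends before the score that made her eligible.

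At stake is the one comparison meant to show whether treated mothers improve more than similar mothers who had home visiting without the study treatment. If some treated mothers contribute untreated or partly treated scores, the contrast does not estimate that difference, and a larger sample would not repair it.

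**Working it through.** The plan gives no power or sample-size figure for this comparison, so there is nothing to reproduce. The check is timeline arithmetic.

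Inputs:
- Reading: 6 months after HV enrollment (Planned analyses). With 365.25 / 7 / 12 = 4.35 weeks per month, this is 26.1 weeks.
- Therapy: 10 weekly sessions (Intervention), so session 10 falls 9 weeks after session 1 if no week is missed.
- Family follow-up: 2 months after the final session (Study measures), that is 9 + 8.7 = 17.7 weeks after session 1.
- *s*: weeks from HV enrollment to session 1. The document does not give it.

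The 6-month reading falls 26.1 − *s* weeks after session 1. Hence:
- **After session 10:** 26.1 − *s* ≥ 9, so *s* ≤ 17.1 weeks (about 3.9 months).
- **During therapy:** 17.1 < *s* ≤ 26.1 weeks. With *s* = 20 the reading is 6.1 weeks after session 1, when 7 of 10 sessions are done. With *s* = 24 it is 2.1 weeks after, when 3 of 10 are done.
- **Before any therapy:** *s* > 26.1 weeks.
- **At or after the 2-month follow-up:** *s* ≤ 26.1 − 17.7 = 8.4 weeks.

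Each week lost to a postponed session lowers the 17.1-week limit by one week.

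Do the eligibility rules keep *s* below 17.1 weeks? They do not. The span from the start of pregnancy to 18 months postpartum is about 40 / 4.35 + 18 = 27.2 months. That span describes maternal stage and not time in the program. It does show that a mother who joined early in pregnancy could still be eligible long after her 6-month mark.

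Does the matching help? Participant selection matches historical mothers on EPDS scores taken at comparable intervals, and on trimester or infant age, among other factors. It does not say from what date the intervals run, and time in the program is not a matching factor. Matching can make the timing alike in the two groups. It cannot move a treated mother's reading to after her therapy.

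**The case against.** The strongest reply concerns weight. This is an exploratory comparison of 12 with 12 in a pilot that the Discussion describes as not powered for statistical differences, and the Limitations section says that the results are not meant to test impact. The first two aims do not use it, and the other third-aim outcomes are tied to therapy. All of this stands and lowers the severity. It does not remove the point, because the analysis section still attaches an effectiveness criterion to the comparison.

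The HV-enrollment clock also has a rationale: historical mothers have no session 1, and program enrollment is a date that both groups share. That explains the choice, but a qualifying screen is also available in both groups.

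The wording is open to another reading. It could be limited to mothers already treated by month 6, or could describe treatment received at that time. No other section schedules treatment then or restricts the comparison in that way, so the sentence would need rewriting on either reading.

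Three stronger readings are tempting, and the document does not support them:
- *Half or more of the treated mothers would be read before therapy.* This depends wholly on assumed tenure. If tenure at session 1 were spread evenly over 0 to 6 months, about 66% would be read after session 10, 34% during therapy and none before. Over 0 to 12 months the split would be about 33%, 17% and 50%. The caseload size and the maternal-stage window say nothing about tenure; a mother 12 months postpartum may have just enrolled.
- *The effect is diluted towards zero by a known amount.* That needs mothers read before therapy to behave like the historical group. Late starters are selected on a later EPDS of 8 or more. A mother who first screened positive after month 6 could have a low 6-month score that looks like benefit.
- *The 6-month reading contradicts the third aim.* The aim speaks of "preliminary impacts of the treatment on maternal depressive symptoms and parental empathy, and family emotion regulation and family functioning at 2 months post-intervention", but the hypothesis about previously enrolled mothers carries no time point. A separate time for a comparison from program records is not in itself a contradiction.

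**Conclusion.** The point holds as a flaw in a stated rule, not as missing detail, because the article itself fixes the anchor. The 6-month reading is a post-treatment outcome only for mothers who start within about 17 weeks of HV enrollment. It is a mid-treatment reading for starts in about weeks 17 to 26 and a pre-treatment reading after that. These limits assume uninterrupted weekly sessions and otherwise use only the document's figures.

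How many of the 12 treated mothers are affected cannot be computed, and could be none if all of them start early; no criterion ensures that they do. Dilution is the simple case, but the direction of bias is not certain. Severity is moderate.

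**What to change.** In Planned analyses, replace the HV-enrollment anchor with an index date defined in the same way for both groups. The qualifying EPDS of 8 or more is preferable: the treated mother's screen before study entry, and the historical mother's matched screen. Both groups are then selected on the same kind of score at the start of the interval.

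Compare EPDS change from that score over one fixed interval with a stated window. The interval must cover the lag from the screen to session 1 plus at least the 9 weeks to session 10. The document does not give that lag, so the investigators need to set it. State in Participant selection that the matching intervals run from the same index date, and report HV tenure at index in both groups.

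The cost is a change of wording and the abstraction of EPDS records by a different date. The downside is that routine EPDS dates may not fall on the interval. The article gives no routine EPDS schedule, so a window is needed and some records may fall outside it. With 12 mothers per group, the availability of records near the chosen time should be checked before the interval is fixed.
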